## Abstract

**Background:**

Despite treatment with highly effective antimalarial drugs, malaria annually claims the lives of over half a million children under 5-years of age in sub-Saharan Africa. Cerebral malaria (CM), defined as *Plasmodium falciparum* infection with coma, is the severe malaria syndrome with the highest mortality. Studies in the CM mouse model suggest that a T cell-mediated response underlies CM pathology, opening a new target for therapy in humans. This trial aims to establish the preliminary safety of one such novel therapy, the glutamine antagonist 6-diazo-5-oxo-L-norleucine (DON).

**Methods:**

In this phase I/IIa dose-escalation clinical trial, a single dose of intravenous (IV) DON is administered to three participants groups—healthy adults and adults with uncomplicated malaria, then pediatric participants with CM—to primarily assess safety. The secondary objective of this trial is to assess pharmacokinetics of DON over a range of doses. The open-label adult portion of the trial enrolls 40 healthy adults concurrently with 40 adults with uncomplicated malaria. Cohorts of 10 participants receive a single IV dose of DON with doses escalating between cohorts from 0.1 mg/kg, 1.0 mg/kg, 5.0 mg/kg, to 10 mg/kg. Following subsequent safety review, a randomized, double-blind, and placebo-controlled pediatric study enrolls 72 participants aged 6 months to 14 years with CM. The pediatric portion of the study minimally spans three malaria seasons including a planned interim analysis after 50% of pediatric enrollments. The first half of pediatric participants receive DON 0.1 mg/kg, 1.0 mg/kg, or placebo. Dosing for the second half of pediatric participants is informed by the safety and preliminary efficacy results of those previously enrolled. The pediatric portion of the study has an exploratory outcome evaluating the preliminary efficacy of DON. Efficacy is assessed by diagnostics predictive of CM outcome: electroencephalography (EEG), magnetic resonance imaging (MRI), and transcranial doppler (TCD), measured before and after DON administration. All participants with malaria receive standard of care antimalarials in accordance with local guidelines, regardless of study drug dose group.

**Discussion:**

This preliminary safety and efficacy study evaluates DON, a candidate adjunctive therapy for pediatric CM. If results support DON preliminary safety and efficacy, follow-up phase II and III clinical trials will be indicated.

**Trial registration:**

This trial was registered on ClinicalTrials.gov on 28 July 2022 (NCT05478720).

## Administrative information

Note: the numbers in curly brackets in this protocol refer to SPIRIT checklist item numbers. The order of the items has been modified to group similar items (see http://www.equator-network.org/reporting-guidelines/spirit-2013-statement-defining-standard-protocol-items-for-clinical-trials/).

## Introduction

### Background and rationale {6a}

Cerebral malaria (CM), defined as an otherwise unexplained coma in someone with *Plasmodium falciparum (Pf)* parasitemia, is the most lethal form of severe malaria [1, 2]. Ninety percent of CM mortality occurs in children, the vast majority of whom are less than 5 years old [3]. Despite treatment with the highly effective anti-malarial, intravenous (IV) artesunate, mortality rates are 15–25%, and children who survive often suffer severe neurological sequalae. At present, there are no predictive diagnostics for which children with malaria will develop CM nor therapy for CM after children progress to severe disease. Thus, the public health burden is enormous.

Current knowledge of the cellular and molecular mechanisms that underlie CM disease pathology are incomplete. The observation of heavily infected red blood cell (iRBC) sequestration in the cerebral vasculature of children who died of CM, often accompanied by intra- and peri-vascular pathology including ring hemorrhages, led to the generally accepted hypothesis that iRBC sequestration in the cerebral vasculature and the resulting mechanical obstruction lead to inflammation, impaired vasoregulation, and blood brain barrier (BBB) dysfunction thus causing this severe progression of malaria [4]. Therapies targeting the purposed downstream effects of sequestration were investigated in multiple clinical trials [5–19], but none improved clinical outcomes. These failures suggested that the downstream effects of iRBC sequestration were poor targets of therapies.

Studies in the mouse model of CM (referred to as experimental cerebral malaria or ECM) provided strong evidence for the role of parasite specific CD8^+^ T cells in the pathology of CM [20]. CD8^+^ T cells had not been targeted for CM therapy in humans, in part, because they had not been reported in the cerebral vasculature of children who died of CM [21, 22]. We recently provided definitive evidence for the presence of CD8^+^ T cells lining the cerebral vasculature in children who died from CM [23]. Our findings point to a mechanism by which CD8^+^ T cells function in disease pathophysiology based on the extraordinary similarities in the distribution of CD8^+^ T cells in the brains of children with CM and in mice with ECM. These observations open new avenues for treatment of CM that involve modulating CD8^+^ T cells with the wealth of available T cell targeting therapeutics.

This clinical trial aims to establish the preliminary safety and efficacy of one such novel therapy, 6-diazo-5-oxo-L-norleucine (DON), a glutamine antagonist. DON has a potent inhibitory effect on a variety of glutamine utilizing pathways including those involved in T cell metabolism. We showed that DON is highly efficacious in treating ECM in mice late in the disease when it has progressed to a point where significant brain swelling and BBB dysfunction have occurred [24]. DON both blocks the progression of ECM and promotes recovery [24, 25]. In a separate study, we used magnetic resonance imaging (MRI) to longitudinally monitor responses to treatment in mice with ECM. We found disease progression mirrored that observed in MRI studies in children with CM, and that, in mice, DON treatment resolved severe brain swelling, which is highly predictive of a fatal outcome [25, 26].

This is not the first clinical trial of DON in humans. DON safety in adults and children with cancer was established in phase I and II clinical trials performed over 40 years ago but did not enter therapeutic use due to a lack of consistent anti-tumor efficacy [17, 27–40]. Most of these studies were multi-dose, covered a wide range of DON treatment regimens, and all were in patients who had failed primary anti-cancer treatment courses. The most commonly reported adverse effects in these studies were nausea and vomiting. However, DON was not evaluated in a single dose, dose-escalation study with concomitant pharmacokinetic (PK) analysis. Therefore, before proceeding to efficacy trials of DON for treatment pediatric CM, we first evaluate DON’s safety in healthy Malawian adults and Malawian adults with uncomplicated malaria before moving to the target population, critically ill children with CM. In the dose-escalation phase I/IIa trial described herein, participants are premedicated with an antiemetic to prophylactically target the most common adverse effects. We will determine the safety profile and PK of a single dose of DON in healthy adult participants and adults with uncomplicated malaria over a dose range of 0.1 mg/kg to 10 mg/kg before assessing safety and efficacy in children with CM.

### Objectives {7}

The primary objective of this study is to evaluate the safety of a single IV dose of DON in healthy adults, adults with uncomplicated malaria, and children 6 months to 14 years old with World Health Organization (WHO) defined CM. Our secondary objective is to determine the PK profile of a single dose of DON administered to an individual at one of four doses studied. Our exploratory objectives are to both determine the preliminary efficacy of DON and to explore the metabolic mechanism(s) of action of DON in children with CM. We hypothesize that a single dose of DON will be safe and tolerable in healthy adults, adults with uncomplicated malaria, and children with CM over the studied dose ranges. We evaluate increasing doses of DON using preliminary markers of efficacy in children with CM, namely changes in patterns on continuous electroencephalography (cEEG), improved MRI brain volume scores, and improved flow velocities on transcranial doppler (TCD) all of which have been previously established as prognostic biomarkers associated with CM mortality [26, 41, 42].

### Trial design {8}

This is a phase I/IIa dose-escalation clinical trial. DON is tested first in adults and then in pediatric participants to evaluate safety. In all participants, after baseline assessments and safety laboratory studies are complete, a single IV dose of DON is administered. The open-label adult portion of the trial concurrently enrolls 40 healthy adults and 40 adults with uncomplicated malaria. Within each of the two adult participant groups, cohorts of 10 participants receive a single IV dose of DON with dose escalation after study team safety review, from 0.1 mg/kg, 1.0 mg/kg, 5.0 mg/kg, to 10 mg/kg. The subsequent study in children with CM is randomized, double-blinded, and placebo-controlled. DON or placebo is administered to participants who also receive standard-of-care CM treatments including IV artesunate. Only doses of DON with a favorable safety profile in adults may be administered to pediatric participants. Four pediatric cohorts (cohorts 1–4) are enrolled, comprising up to 72 participants with CM aged 6 months to 14 years. Peak transmission occurs during the rainy season in Malawi, which is typically January–June. Anticipated enrollment spans at least three malaria seasons. Pediatric participants in cohorts 1 (*N* = 6, 8%) and 2 (*N* = 12, 17%) receive DON 0.1 mg/kg or placebo. Pediatric cohort 3 (*N* = 18, 25%) receives DON 1.0 mg/kg or placebo. Upon completion of cohorts 1–3, 50% of pediatric enrollment, there is an interim safety analysis. The remaining 50% of pediatric participants are enrolled in pediatric cohort 4. Dosing in cohort 4 is informed by both the adult safety data and the interim analysis of pediatric safety and exploratory efficacy data. Dosing may remain at the two lower doses of DON (0.1 mg/kg and 1.0 mg/kg) or may escalate to higher doses pending safety and preliminary efficacy results in children previously enrolled and regulatory review amendment approval. The duration of study for each participant is six months (Fig. 1).

**Fig. 1 Fig1:**
[figure not shown]
Schematic of study design for the adult (**A**) and pediatric (**B**) enrollment. Pharmacokinetic (PK); severe adverse events (SAEs); adverse events (AEs); continuous electroencephalogram (cEEG); magnetic resonance imaging (MRI); transcranial doppler (TCD); lumbar puncture (LP); post-intervention (p.i.)

## Methods: participants, interventions and outcomes

### Study setting {9}

This study is conducted in Blantyre, Malawi. Adults are enrolled at the Ndirande Research Clinic. Pediatric enrollments will occur on the Pediatric Research Ward (PRW) at Queen Elizabeth Central Hospital (QECH), the main referral hospital in the Southern Region of Malawi.

### Eligibility criteria {10}

Healthy adults are eligible for enrollment if they are not acutely ill and do not meet any exclusion criteria, including pregnancy, lactation, or current highly active antiretroviral (HAART) or anti-tuberculosis medication use (Table 1). Adults with uncomplicated malaria are enrolled if they have been diagnosed with malaria in the last 24 h, are febrile or have a history of fever, have a positive malaria thick blood smear, have a normal mental status, and are not taking any of the excluded medications mentioned previously. Children with CM are considered for enrollment if they have WHO defined CM: coma (defined as a Blantyre coma score (BCS) ≤ 2), a positive rapid diagnostic test or peripheral blood smear positive for malaria, and no other known causes of coma (Table 1). In all participants, screening and eligibility evaluations will be completed in less than 6 h.

**Table 1 Tab1:** Inclusion and exclusion criteria for healthy adults, adults with uncomplicated malaria and children with cerebral malaria

	**Healthy adults**	**Adults with uncomplicated malaria**	**Children with cerebral malaria**
**Inclusion criteria**	Age ≥ 18 years old	Age ≥ 18 years old	Age 6 months–14 years old
	Informed consent obtained and informed consent form (ICF) signed	Informed consent obtained and ICF signed	Informed consent obtained and ICF signed by parent or guardian
	Temperature ≤ 37.5 °C	Temperature ≥ 38 °C or history of fever in the past 24 h	Temperature ≥ 38 °C or history of fever in the last 24 h
	Hemoglobin ≥ 7 g/dL or hematocrit/ packed-cell volume (PCV) ≥ 20%	Hemoglobin ≥ 7 g/dL or hematocrit/PCV ≥ 20%	Hematocrit or PCV ≥ 18%
	Thick or thin blood smear **negative** for asexual forms of *P. falciparum*	Thick or thin blood smear **positive** for asexual forms of *P. falciparum* (parasite count and speciation documented)	Thick or thin blood smear **positive** for asexual forms of *P. falciparum* or positive malaria rapid diagnostic test
	Negative pregnancy test for persons of child-bearing potential (9–59 years)	Negative pregnancy test for persons of child-bearing potential (9–59 years)	Negative pregnancy test for persons of child-bearing potential (≥ 9 years)
	Body mass index (BMI) 18.5–30 kg/m^2^	BMI 18.5–30 kg/m^2^	Blantyre coma score ≤ 2
	Creatinine: ≤ 110 mmol/L / ≤ 1.2 mg/dL (males) or ≤ 90 mmol/L / ≤ 1.0 mg/dL (females)	Creatinine: ≤ 110 mmol/L / ≤ 1.2 mg/dL (males) or ≤ 90 mmol/L / ≤ 1.0 mg/dL (females)	No other explanation for coma by history or physical exam
		Glasgow coma score of 15	
		Respiratory rate ≤ 20 breaths/minute	
		Oxygen saturation ≥ 90% on room air	
**Exclusion criteria**	Pregnancy or lactation	Pregnancy or lactation	Pregnancy or lactation
	Allergy to ondansetron	Allergy to ondansetron	Allergy to ondansetron or ceftriaxone
	Currently taking highly active antiretroviral therapy (HAART)	Currently taking HAART	Currently taking HAART
	Currently taking anti-tuberculosis medications	Currently taking anti-tuberculosis medications	Currently taking anti-tuberculosis medications
	Participants attempting to become pregnant	Participants attempting to become pregnant	Cloudy cerebrospinal fluid (probable bacterial central nervous system infection)
			Malnutrition > 3 standard deviations below the mean weight for height and/ or mid-upper arm circumference ≤ 11.5 cm

### Who will take informed consent? {26a}

Study nurses pre-screen potential study participants using an eligibility checklist. Adults or parents/guardians of pediatric potential participants are given a brief description of the study and, if interested in enrolling, are referred to either the Ndirande Research Clinic (adults) or PRW (children) for informed consent. Study nurses read the informed consent form (ICF) together with the potential adult participants or parents/guardians of potential pediatric participants. Key information about the study’s purpose, procedures and experimental aspects, risks and discomforts, expected benefits to the participant or to their parents/guardians, and alternative treatments (in pediatric participants, no adjunctive therapy) are reviewed. Adult participants and parents/guardians of pediatric participants sign the ICF before initiating study procedures. Minors will not be approached for assent as they are comatose and gravely ill at recruitment.

### Additional consent provisions for collection and use of participant data and biological specimens {26b}

The ICF includes information on possible analysis of participant biological specimens. Adult participants and parents/guardians of child participants will decide if they want any residual biological specimens destroyed or stored for possible future research at the end of the trial. The decision to participate in the storage of residual biological specimens can be changed at any time by notifying the study team.

## Interventions

### Explanation for the choice of comparators {6b}

The adult portion of the study does not have a comparator group. In contrast, the pediatric portion of the trial is placebo controlled to provide a comparator for exploratory efficacy endpoints. Placebo is normal saline in syringes identical to those used to deliver DON. Placebo is used because no approved treatment for CM yet exists.

### Intervention description {11a}

Individually packaged 200 mg or 10 mg fill vials of DON are stored frozen at –20 °C. Before administration, DON is removed from the freezer and allowed to reach room temperature over 30 min. Thawed DON is then reconstituted with 10 mL of normal saline. The reconstituted product is shaken to resolubilize, and a weight-specific volume of the active product is drawn up into an appropriately sized syringe. Thirty minutes after premedication with the antiemetic ondansetron, the intervention is infused IV over 10 min.

Within each of the two adult participant groups, healthy and uncomplicated malaria, the first 10 participants enrolled receive DON 0.1 mg/kg IV. If this dose is proven safe and tolerable, the subsequent cohorts of 10 participants in each adult group receive DON 1.0 mg/kg IV, 5.0 mg/kg IV, or 10.0 mg/kg IV, sequentially. In pediatric participants, we administer a single IV dose of DON with interim safety reviews. In cohort 1, we enroll 6 participants, randomized 2:1 to either DON 0.1 mg/kg or placebo. If no halting criteria (as described the “Criteria for discontinuing or modifying allocated interventions {11b}” section) are met, we continue to cohort 2 of pediatric recruitments in which 12 participants will be randomized 5:1 to receive DON 0.1 mg/kg or placebo, respectively (randomization ratio for DON 0.1 mg/kg or placebo of 7:2 cohort when combining cohorts 1 and 2). If the risk–benefit profile is promising, the study continues to cohort 3 of pediatric recruitment. In cohort 3, 18 pediatric participants receive either DON 1.0 mg/kg or placebo at a ratio of 7:2, respectively. Subsequent dose escalation above 1.0 mg/kg in pediatric participants are informed by safety and tolerability in the adult cohorts and in the first three pediatric cohorts and will not proceed without regulatory review. The doses in pediatric cohort 4 (*N* = 36) participants may either remain the same (DON 0.1 mg/kg, and 1.0 mg/kg), include one of the same doses, and/or include higher doses against placebo at an anticipated randomization ratio of 7:7:4 (DON dose 1: DON dose 2: placebo) subject to regulatory review and approval.

### Criteria for discontinuing or modifying allocated interventions {11b}

#### Adults

Dose-escalation in cohorts of adult participants halts if more than four of the 10 subjects in a dosing cohort have related grade 2 and 3 adverse events (AEs) or severe adverse events (SAEs), if there are related SAEs within any dose, or if there is an overall pattern of symptomatic, clinical, or laboratory events that the Pharmacovigilance Group within the Division of Microbiology and Infectious Diseases (DMID) or the Data and Safety Monitoring Board (DSMB) considers associated with the study product. The study will stop enrollment and describe findings to the independent safety monitors (ISM) and the DMSB to evaluate future dose escalation. At the end of adult enrollments, all safety data are reported to the DSMB to inform dose ranges to be studied in children with CM. The DMID medical monitor may stop enrollment and/or administration of study product if AEs meeting the halting criteria are reported.

#### Pediatric

We begin cohort 1 with 6 pediatric participants who receive the lowest dose of DON 0.1 mg/kg (*N* = 4) or placebo (*N* = 2). Barring significant SAEs triggering halting rules, we proceed to cohort 2 and enroll the remainder of the participants in the DON 0.1 mg/kg dose group with participants again randomized to DON 0.1 mg/kg (*N* = 10) or placebo (*N* = 2). If the number and type of SAEs incurred in cohort 1 and 2 do not meet study halting rules, we dose escalate in cohort 3 to DON 1.0 mg/kg (*N* = 14) or placebo (*N* = 4). After cohorts 1–3 of pediatric recruitment, an interim analysis will assess all safety and efficacy endpoints. If the benefit-risk profile is promising, the study continues to cohort 4 of pediatric recruitments. Based on the safety, pharmacokinetic, and preliminary efficacy profiles of the doses administered in cohorts 1–3, the dose(s) for participants in cohort 4 are determined after the interim analysis. The DSMB will meet after the completion of cohort 3 (50% of pediatric enrollment), and as needed for any study safety issue.

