#### Pediatric halting rules

The pediatric study pauses enrollment if the number of participants with SAEs in any single MedDRA group exceeds rates expected in children with CM. The expected rates were derived from calculating the cumulative probability of stopping when the true rate of the proportion of participants in a specific MedDRA classification group is a given percent (i.e., 25, 30, 40 or 50%). For example, 9 participants out of the first 17 enrolled must have an SAE within a single MedDRA classification group for the study to pause for review. (This will indicate a single important toxicity that should be considered before further enrollments.) A halt is not triggered, however, if of the first 17 enrolled pediatric participants, 9 experience SAEs in different MedDRA classification groups (e.g., 3 participants die, 3 participants have renal failure, and 3 participants have severe thrombocytopenia). High rates of both adverse outcomes and abnormal laboratory values are expected in pediatric CM. Therefore, only single recurring SAEs within a MedDRA classification group will initiate a pause for safety review. The properties for the halting rules were estimated by Monte Carlo simulation with 100,000 replicates. At any halt, the DSMB will review the data and evaluate whether the study should stop due to safety concerns.

Although we will only report SAEs to the regulatory bodies that have a reasonable possibility of being related to the intervention, for the purpose of applying halting rules, all events (deaths, disability, etc.), even if not specifically reported as SAEs related to treatment, will be documented.

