## Assignment of interventions: blinding

### Who will be blinded {17a}

Evaluators of safety and efficacy outcomes including study clinicians and nursing staff, as well as study participants and their parents/guardians, are blinded to the randomization assignment for pediatric participants.

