### Composition of the data monitoring committee, its role and reporting structure {21a}

Safety oversight is conducted by a DSMB. The DSMB consists of at least three voting members, including a biostatistician experienced in statistical methods for clinical trials and a clinician with relevant expertise, who do not have scientific, financial, or other conflict of interest related to this study. The DSMB operates under the rules of a sponsor-approved charter. The DSMB reviews unblinded enrollment and demographic information, medical history, concomitant medications, physical assessments, clinical laboratory values, dosing compliance, and solicited and unsolicited AEs/SAEs on a regular basis and as needed during this trial. The DMID medical monitor and ISM (as deemed necessary) review SAEs in real time. As an outcome of each review meeting, the DSMB makes a recommendation on the decision to proceed with dose escalation, and to continue, modify, or terminate this trial.

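### The protocol states different conditions for the pediatric step from 0.1 to 1.0 mg/kg and does not say which governs; the weaker one can be met with a high count of children with any SAE

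*Protocol article*

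**What the plan says.** All references are to the protocol article.

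- **Section {11b}, Pediatric**, on the step to cohort 3: "If the number and type of SAEs incurred in cohort 1 and 2 do not meet study halting rules, we dose escalate". This section places its benefit-risk test later, before cohort 4. On DSMB timing it says: "The DSMB will meet after the completion of cohort 3 (50% of pediatric enrollment), and as needed for any study safety issue".
- **Section {11b}, Pediatric halting rules**: a pause needs enough children with an SAE in one MedDRA group, for example 9 of the first 17. "A halt is not triggered, however, if of the first 17 enrolled pediatric participants, 9 experience SAEs in different MedDRA classification groups". On referral: "At any halt, the DSMB will review the data and evaluate whether the study should stop due to safety concerns".
- **Section {11a}**, on the same step: "If the risk–benefit profile is promising, the study continues to cohort 3 of pediatric recruitment". It names no body to judge this. For the step from cohort 1 to cohort 2 the same section asks only that no halting criterion is met. It also mentions interim safety reviews in children, without timing or reviewer.
- **Section {21a}**: the DSMB reviews unblinded data regularly and as needed, and after each review meeting "the DSMB makes a recommendation on the decision to proceed with dose escalation". In addition, "The DMID medical monitor and ISM (as deemed necessary) review SAEs in real time".
- **Section {17a}**: "Evaluators of safety and efficacy outcomes including study clinicians and nursing staff, as well as study participants and their parents/guardians, are blinded".
- **Primary endpoints**: for children, any SAE within 14 days of dosing.
- **Section {14}**: exact 90% intervals for the SAE rate, worked out for the 14 DON recipients of cohorts 1 and 2, with a 20% background rate.

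**The concern.** One decision, whether to raise the dose tenfold in comatose children, carries different conditions in different sections. A team working from the pediatric part of {11b} would go on when no halting rule is met. A team working from {11a} would also have to judge risk against benefit. Section {21a} points to the DSMB for a recommendation, but no DSMB review is tied to this step.

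The difference matters because the halting rules do not use the quantity that defines the primary endpoint. They look for one recurring toxicity, whereas the primary endpoint counts children with any SAE. A moderate excess in several organ systems raises the second and may leave the first untouched. The stated adult rule does count across event types and has an overall-pattern clause that the DSMB can invoke; the stated pediatric rule has neither. The clinicians and outcome evaluators are blinded, so the DSMB is the body described as seeing events by arm. If the weaker condition governs, cohort 3 could open before anyone charged with recommending on escalation has considered the any-SAE count at 0.1 mg/kg.

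**Working it through.** **1. The conditions side by side**

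| Step | Section {11a} | Section {11b}, Pediatric | Section {21a} |
|---|---|---|---|
| Cohort 1 to 2 | No halting criterion met | No SAEs that trigger the halting rules | – |
| Cohort 2 to 3 (0.1 to 1.0 mg/kg) | Promising risk-benefit profile | Halting rules not met | DSMB recommends on escalation after its review meetings |
| Cohort 3 to 4 | Higher doses rest on safety so far and regulatory review | Promising benefit-risk profile; DSMB meets | DSMB recommends, as above |

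Section {11a} changes its test between the first and second steps. Section {11b} keeps the same test for both and moves the benefit-risk test one step later. No section ranks the conditions or says that they are cumulative.

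**2. The plan's own precision figure for cohorts 1 and 2**

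Inputs from section {14}: n = 14 on DON, background rate 20%, exact 90% central interval. The upper Clopper-Pearson limit for x events is the 0.95 quantile of Beta(x + 1, n − x). For x = 4 it is 0.540. P(X ≤ 4 | 14, 0.20) = 0.870. This reproduces the stated power of over 85% and the 54% limit. The any-SAE calculation for this decision point therefore exists, but {11b} ties no decision to it.

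**3. How unusual is a count that causes no halt?**

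The article's example is 9 of 17 children with SAEs in different groups. For a true any-SAE rate p, P(X ≥ 9 | 17, p) is the sum over k = 9 to 17 of C(17, k) p^k (1 − p)^(17 − k).

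| p | 20% | 25% | 30% | 35% | 40% |
|---|---|---|---|---|---|
| P(X ≥ 9 of 17) | 0.3% | 1.2% | 4.0% | 9.9% | 19.9% |

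The 20% is the planning rate of section {14}. The rest is a range, because section {6a} puts mortality alone at 15–25%, so the any-SAE background may exceed 20%. At the planning rate such a count would be a strong signal. At 40% it would be unremarkable, so the count needs judgement.

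**4. How weak is the condition of not halting? Illustration only**

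Assumptions: one look at 17 children; 13 on DON with a true any-SAE rate of 54% (the limit in step 2) and 4 on placebo at 20% or 30%; at most one SAE group per child; three groups with assumed splits; pause if any group reaches 9. Simulation with 1,000,000 replicates, except the last row, which is an exact convolution of the two binomials.

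| Split of SAEs over groups | Pause, placebo 20% | Pause, placebo 30% |
|---|---|---|
| Equal thirds | 0.1% | 0.1% |
| 50/25/25 | 0.6% | 0.9% |
| 70/15/15 | 6% | 8% |
| All in one group | 36% | 44% |

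Under these assumptions the result depends strongly on how the SAEs are spread.

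**5. What the DSMB would see after cohort 2**

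Exact 90% intervals for n = 14 on DON: 4 events, 10–54%; 6 events, 21–67%; 8 events, 33–79%. For placebo, 1 of 4 gives 1–75%, so placebo is context only. A cut-off would be fragile. P(X ≥ 6 of 14) is 4% at a true rate of 20%, 11% at 25%, 22% at 30%, 51% at 40% and 87% at 54%.

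**The case against.** The strongest reply is that the conditions can hold together: no halting rule met, a promising profile, and a DSMB recommendation. Nothing in {11b} excludes the DSMB or calls escalation automatic. Section {21a} gives the DSMB the escalation role, and 0.1 to 1.0 mg/kg is the one escalation in the blinded part planned without a further regulatory review, so it is a natural target of that sentence. Regular and as-needed DSMB reviews, the interim safety reviews of {11a} and the medical monitor's real-time SAE review could all bring a look before cohort 3. Only doses with a favorable adult safety profile may be given to children, and the DSMB receives all adult data, planned up to 10 mg/kg. The meeting calendar may well stand in the DSMB charter or the full protocol, neither of which is shown.

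Most of this stands. A reader might infer that the DSMB has no look before the tenfold step, or that the sections flatly contradict each other. The documents support neither. The regular, as-needed and interim reviews leave room for an earlier look, and a cumulative reading is possible. Nor is the per-group rule a mistake: the article explains it by the high event rates expected in cerebral malaria.

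The pause probabilities also cannot be read as operating characteristics of the rule. The full boundary table is not shown, earlier looks would raise the chance of a pause, as would children with SAEs in several groups, and the splits are assumed.

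What the reply does not settle is which condition governs. The cumulative reading has to be supplied by the reader, and {11b}, taken alone, states the weaker condition as enough.

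**Conclusion.** The point holds as an inconsistency about a safety decision. Sections {11a}, {11b} and {21a} state different conditions for the same step, and the article does not say which one governs or that all must be met. The weakest can be satisfied with 9 of 17 children having an SAE, on the article's own example. No review of the any-SAE count by arm is tied to the step, though one may take place.

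This conclusion rests on the wording and on the article's example, not on the simulated pause probabilities. How alarming 9 of 17 would be depends on the background rate: from 0.3% probability at 20% to 20% at 40%. The existing safeguards reduce the risk. A correction is still worth making, because the step is tenfold, the children are comatose and the needed data are already collected. Confidence is medium, since the charter and the full protocol may already resolve it.

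**What to change.** Keep the per-group halting rule. Amend the pediatric part of section {11b}, and align {11a} and {21a} with it, along these lines: cohort 3 opens only if no halting rule has been met in cohorts 1 and 2 and the DSMB has recommended escalation, having reviewed the number of children with any SAE by arm (14 DON with the exact 90% interval of section {14}, and 4 placebo).

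Set no fixed any-SAE threshold. With 14 children a cut-off would misfire too often across plausible background rates, so the judgement should stay with the DSMB. If the charter already provides this review, a cross-reference in {11b} is enough.

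The cost is one sentence and one table from data already collected, with no added patients or procedures. The downside is a short wait after cohort 2 and possibly a more frequent deferral of escalation.
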